### 11.5.2 Multi-center Studies

This study will be conducted in approximately 9 clinical sites. Descriptive measures will be used to assess whether the treatment effect differs by site for primary and secondary variables, but no formal tests will be conducted.

### 11.5.3 Multiple Comparisons and Multiplicity

The primary formal hypothesis test will be conducted using an alpha on a two-sided test of 0.05. Because only a single hypothesis test will be tested and other reported p-values will be considered descriptive, no adjustment for multiple comparisons will be made. Informal hypothesis tests conducted as a part of secondary analyses will all be two-sided tests, and the p-values from these tests will be presented as descriptive measures of strength of evidence. These descriptive p-values will be presented for differences between treatment groups in summary tables for secondary exploratory analyses.

### 11.5.4 Examination of Subgroups

Primary and most secondary efficacy analyses will be stratified by TRV stratum ( $2.7 \text{ m/s} \leq \text{TRV} < 3.0 \text{ m/s}$ , or  $\text{TRV} \geq 3.0 \text{ m/s}$ ). If warranted, subgroup analyses by TRV stratum may be performed to examine differences in treatment effect. Any subgroup analysis will be performed as an exploratory analysis and represented as such.

### 11.5.5 Handling of Dropouts and Missing Data

Investigators should make every effort to obtain end of study assessments when subjects discontinue from the study due to clinical deterioration.

For the ANOVA, ANCOVA, and the Wilcoxon rank sum test, missing data at the Week 16 assessment will be derived from predefined replacement rules:

- *Last Observation Carried Forward (LOCF)*. Subjects without an assessment at Week 16 due to missing data (e.g. lost to follow-up) will have their last 6MW distance, Borg dyspnea index, and WHO functional classes carried forward (LOCF). Additionally, LOCF will be used for those who discontinue early for any reason, but who participate in a study assessment at the time of withdrawal.
- *Worst measurable value and worst observed value*. A subject who is missing endpoint values at 16 weeks because of discontinuation of study medication due to clinical worsening or death will be assigned values equal to or worse than the worst values recorded in a subject who does not discontinue study medication. Subjects who die will be assigned the worst value possible based on the scale of the endpoint (e.g., 0m for the 6MW, 10 for the Borg dyspnea and FC IV), whereas subjects who discontinue due to clinical worsening and who also do not participate in an end of study assessment of that endpoint will be assigned the worst value from that subject's treatment group and stratum.
- No hemodynamic parameters will be imputed.

No data imputation will be performed for the linear mixed model analyses, and no data will be discarded. For persons who withdrew from treatment early, this type of analyses

have been designed to use the data obtained to the point that they were lost. For these secondary analyses, missing data will be treated as randomly missing data.

## 11.6 Sample Size

This study will randomize 132 subjects (66 to sildenafil and 66 to placebo). Sample size was determined based on the following considerations.

The measurement of primary interest is the change in 6MW distance from baseline to week 16. To estimate the trial sample size for the primary endpoint, we used data from Ghofrani's evaluation of the effects of sildenafil in subjects with chronic thromboembolic pulmonary hypertension. Ghofrani's study showed an average change from baseline of 53.7m in 6MW distance with a standard deviation of 67m after approximately 6 months of sildenafil treatment.

A t-test was used to compare the difference in change from baseline 6MW distance between the sildenafil and placebo treatment groups. In order to calculate the sample size the following assumptions were made:

- No subjects discontinue because of clinical worsening or death
- No subjects dropout prior to week 10 for other reasons
- Sixteen-week change in 6MW distance is normally distributed in both treatment groups
- Sixteen-week change in 6MW distance is 40m in subjects on sildenafil and there is no change in subjects on placebo (i.e., a difference of 40m between the two treatment groups)
- Standard deviation of change from baseline between 62 and 72m for the 16-week change in each of the treatment groups
- Power ranges from 80% to 90%
- Two-sided t-test with  $\alpha=0.05$

Table 6 presents the number of subjects needed per treatment arm for the range of assumed standard deviations and powers, thus the total number is 2 times the numbers presented in each cell.

**Table 6. Sample size needed per treatment arm by assumed standard deviation and power**

| Change from baseline (6MW) | Standard deviation (m) | Power 90% | Power 85% | Power 80% |
|----------------------------|------------------------|-----------|-----------|-----------|
| Mean 40m                   | 62                     | 52        | 45        | 39        |
|                            | 67                     | 60        | 52        | 46        |
|                            | 72                     | 70        | 60        | 52        |

If we choose the standard deviation of change from baseline determined in Ghofrani's study (67m) and a power of 90%, then we would need 60 subjects enrolled per treatment

arm. If the standard deviation were to be larger (e.g. 72m), 60 subjects per treatment arm would still result in 85% power to detect a 40m change in 6MW distance in subjects treated with sildenafil versus 0m change in placebo treated subjects. We anticipate that up to 10% of the subjects may dropout during the randomization phase prior to week 10. In order to maintain study power in the presence of potential study dropouts, we will supplement the computed sample size with an additional 10%. Based on these data, we will randomize 132 subjects into the study (approximately 33 per each of four treatment arm/TRV strata combinations).

The data presented above were also used to develop power calculations under multiple scenarios.

- I. Using the two-sample t-test approach, power estimates were developed with the following assumptions
    - a) 5% of subjects randomized to placebo and 2.5% of subjects randomized to sildenafil will discontinue study medication due to clinical worsening or death, and therefore will have assigned values less than the smallest change in 6MW distance in a subject who completes the study. If 6MW is normally distributed in subjects who complete the study, simulations indicated that the power is still 90%.
    - b) The same result was obtained for percentages discontinuing study medication of 10% and 5% in placebo and sildenafil subjects, respectively.
  - II. The effect of sildenafil on 6MW distance over time was also explored using a General Linear Mixed Model (GLMM) with change from baseline as the outcome variable. The SAS® procedure MIXED was used to fit the GLMM. The GLMM included treatment group and weeks on treatment (as a class variable) as fixed effects, and subject as a random effect. This type of model allows exploration of general trends over time while controlling for correlations between repeated measurements made on each subject. The GLMM indicated a within-subject standard deviation of 47.4m and a between-subject standard deviation of 89.7m across that study. Power was calculated using mixed models under the following scenarios:
    - a) Assumptions:
      - 66 subjects per treatment group,
      - 4 visit time points (Wk6, Wk10, Wk16),
      - within- and between-subject variance components obtained from the mixed model run on the Ghofrani data set,
      - mean change from baseline for the sildenafil group is 15, 25, and 40 at Wk6, Wk10, and Wk16 visit time points respectively,
      - mean change from baseline for the placebo group is 0 at all 3 post-baseline visit time points, and
      - no subjects are lost to follow up (no missing endpoint data)
- Power estimated: 92.8%

- b) Same assumptions as scenario IIa, but instead of zero subjects lost to follow-up we assume that 6% in placebo and 3% in sildenafil group are lost-to-follow-up between Wk6 and Wk10, and 6% in placebo and 3% in sildenafil group are lost between Wk10 and Wk16. All available data is used to compensate for the data missing on a particular subject (no LOCF procedures).  
→ Power estimated: 91.1%
- c) Same assumptions as scenario IIa, but instead of no lost to follow up subjects we assume that 12% in the placebo and 6% in the sildenafil group are lost between Wk0 and Wk6. All available data is used to compensate for the data missing on a particular subject (no LOCF procedures).  
→ Power estimated: 90.6%
- d) Same assumptions as scenario IIa, but we assume that mean change from baseline for the sildenafil group is 10, 20, and 35 at Wk6, Wk10, and Wk16  
→ Power estimated: 84.9%

Now we show that the sample size calculated for the primary endpoint is appropriate for detecting significance in the secondary hemodynamic endpoint (change from baseline PA pressure) using data from the recently completed SUPER-1 trial (a randomized placebo control trial evaluating the effects of 20 mg, 40 mg or 80 mg TID of sildenafil in subjects with PH). Using the hemodynamic data from the 80 mg arm of the SUPER-1 trial with 5% two-sided significance level and 80% power, the N for mean change from baseline PA pressure is 32 subjects per group, for pulmonary vascular resistance the N is 25 subjects per group. Assuming that half of the subjects enrolled in the trial will have moderate to severe PH ( $TRV \geq 3.0$  m/s) and meet criteria for RHC the study will be adequately powered to ascertain the hemodynamic effects of 80 mg sildenafil.

Based on the data described herein, we will randomize 132 subjects into the study (approximately 33 per each of four treatment arm/TRV strata combinations). All randomized subjects will contribute to the primary intent-to-treat (ITT) analysis. Assuming a 15-20 % incidence of PH (defined by  $TRV \geq 2.7$  m/s) in adults with sickle cell disease, approximately 1000 subjects will have to be screened for eligibility to ensure a sufficient number of subjects with  $TRV \geq 2.7$  m/s. Subjects will be stratified and randomized for each TRV stratum and treatment arm ( $\geq 2.7$ - $2.9$  m/s and  $\geq 3.0$  m/s) with 66 subjects assigned to each treatment.

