RhoRAND will be configured to send alerts to the project administrative team when numbers in a stratum approach 66. Based on power calculations, a minimum of 64 subjects with  $TRV \geq 3.0$  m/s should be randomized. Additionally, slight over-enrollment in the  $2.7 \text{ m/s} \leq TRV < 3.0 \text{ m/s}$  stratum may be permitted by NHLBI, if funding is available at that time.

To preserve the scientific integrity of the MIT, all subjects will remain blinded to their MIT treatment assignment until after the MIT database is locked.

Pharmacists at each site will be blinded and will utilize the blinded randomization notification from RhoRAND to issue appropriate study drug to each randomized subject. The RhoRAND system is able to provide unblinding information in case of a medical emergency where the exact study drug is needed in order to appropriately treat a subject. This information can only be accessed by a pre-authorized individual, such as the medical monitor.

The subjects, physicians, nurses, and ancillary support staff will be blinded to individual treatment assignment. The placebo formulations will be identical in appearance and taste to the active compounds (see Section 8.1).

The mechanism for unblinding in a clinical emergency will be detailed in the Manual of Operations.

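### The PA-pressure requirement of 32 per group has no stated allowance for missing Week 16 catheterisations; with 10% missing, the planned 66 gives about 77% unadjusted power (minor)

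*Protocol*

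**What the plan says.** Right heart catheterisation at baseline and Week 16 is confined to subjects with TRV of at least 3.0 m/s, expected to be half of the 132, or about 33 per arm.

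- **Section 11.6, haemodynamic sample size:** "the N for mean change from baseline PA pressure is 32 subjects per group". This is set at 80% power and a two-sided 5% level, from the 80 mg arm of an earlier placebo-controlled sildenafil trial. The requirement for vascular resistance is smaller, at 25 per group. On the assumption that half the subjects qualify for catheterisation, the section concludes that the study is adequately powered for haemodynamic effects. No dropout condition is attached.
- **Section 11.6, dropout:** "We anticipate that up to 10% of the subjects may dropout during the randomization phase prior to week 10". A 10% supplement follows, taking the walk-distance requirement from 60 to 66 per arm. None is stated for haemodynamics.
- **Section 6:** a recruitment floor applies to the stratum with the higher TRV: "Based on power calculations, a minimum of 64 subjects with". The randomisation system sends an alert as either stratum nears 66.
- **Section 11.5.5:** "No hemodynamic parameters will be imputed". Walk distance, by contrast, has last-observation and worst-value rules.
- **Section 11.2.2:** continuous secondary outcomes, haemodynamic parameters among them, are analysed with models like the primary one, of both ANOVA and ANCOVA type.
- **Section 7.1 and Table 4:** end-of-study assessments are requested, as far as possible, when study drug stops early, and the early-termination column includes catheterisation.

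**The concern.** A change from baseline in PA pressure needs two catheterisations, and nothing replaces a missing second one. The natural reading of 32 per group is therefore 32 subjects with paired values. The protocol accepts that dropout costs power and allows for it on the endpoint that imputation protects, but states no allowance on the endpoint that imputation does not protect.

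Section 6 then uses the analysis number as a recruitment minimum: 64 randomised is 32 per arm before any loss. The planned 33 per arm leaves one spare subject per arm, about 3% (1 − 32/33), against an expected loss of up to 10%.

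At stake is the accuracy of a power statement that also sets an operational minimum. A reader of an inconclusive PA-pressure result should know how much power the trial could be expected to have.

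**Working it through.** **Inputs.** From section 11.6: two-sided α = 0.05, 80% power, 32 per group for PA pressure, 25 per group for pulmonary vascular resistance, dropout up to 10%. From section 6: minimum 64, 1:1 allocation. From sections 4.4.2.4 and 11.6: about 33 per arm planned in this stratum.

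**Check of the method.** A two-sample t-test with a 40 m difference reproduces all nine cells of Table 6: 52/45/39 at SD 62, 60/52/46 at SD 67 and 70/60/52 at SD 72. The normal approximation gives one fewer in each cell. The t-test is therefore used below.

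**The 32 itself.** It cannot be rebuilt, because the protocol names its source trial but prints neither a difference nor an SD for PA pressure. The effect is back-solved instead.

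- Solve power(d, n = 32 per arm, α = 0.05) = 0.80. Result: d = 0.711.
- For vascular resistance, solve the same equation at n = 25. Result: d = 0.809.

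**Numbers after 10% loss.**

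- Planned 66: 33 × 0.9 = 29.7 per arm.
- Minimum 64: 32 × 0.9 = 28.8 per arm.

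**Power for change in PA pressure, unadjusted t-test, d = 0.711.**

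| Randomised in stratum | All pairs complete | 10% lack the second catheterisation |
|---|---|---|
| 66 (33 per arm) | 81.2% | 76.9% (29.7 per arm) |
| 64 (32 per arm) | 80.0% | 75.6% (28.8 per arm) |

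**Sensitivity to rounding.** If 32 was rounded up from just over 31, d is about 0.723. The figures at 10% loss become 78.2% (66 randomised) and 76.9% (64 randomised), still below 80%.

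**Sensitivity to the loss rate.** Ten per cent is the protocol's upper figure. At 5% loss, 66 randomised leaves 33 × 0.95 = 31.35 per arm, giving 79.2%.

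**Pulmonary vascular resistance, d = 0.809.** 85.4% at 28.8 per arm and 86.5% at 29.7 per arm. The 25 per group leaves ample room for the same loss.

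**The case against.** Four points on the other side have force.

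1. **The plan is 66, and 10% is a ceiling.** A reader might take 76% as the power of the plan. It is not: that figure combines the minimum of 64 with the largest anticipated dropout and assumes that every leaver lacks a second catheterisation. About 77% is the relevant figure at 10% loss, and 79% at 5%.

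2. **Dropout is not the same as a missing catheterisation.** Table 4 and section 7.1 ask for end-of-study assessments at early termination where possible, so some leavers may supply a pair. This stands in part. Under the titration schedule, someone leaving before week 10 has not reached the 80 mg step to which the section 11.6 claim refers.

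3. **The planned models may recover the loss.** Section 11.2.2 already provides ANCOVA-type models for haemodynamics. If these adjust for the baseline value, as the primary model does, and variances are equal, the residual variance relative to a change score is (1 + ρ)/2, where ρ is the baseline-to-Week-16 correlation. The protocol gives no ρ. With 66 randomised and 10% loss, power is 83.2% at ρ = 0.7, 81.1% at 0.8 and 79.0% at 0.9. With 64 it is 82.1%, 79.9% and 77.7%. The shortfall is therefore established only for the unadjusted comparison.

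4. **Little depends on it.** Sections 11.2.2 and 11.5.3 treat secondary tests as informal and their p-values as descriptive.

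A reader might also infer that the protocol made an arithmetic error, or that the trial is underpowered for haemodynamics generally. Neither is supported. The 32 cannot be recomputed from what is printed, 33 per arm does exceed 32, no numeric power after losses is promised, and vascular resistance keeps more than 80%. What remains is that the adequacy claim and the minimum of 64 are stated with no condition on paired data, although the protocol itself anticipates losses.

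**Conclusion.** The point holds as a minor one. On an unadjusted change-score comparison, the planned 66 gives about 81% power for PA pressure if all pairs are complete and about 77% if 10% lack the second catheterisation. The minimum of 64 gives 80% and about 76%. Measured against 80%, the shortfall at 10% loss is about 3 points at the planned number (80 − 76.9) and 4.4 points at the minimum (80 − 75.6).

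This rests on three assumptions: that 32 per group means subjects with paired values and contains no hidden margin; that the effect is the one implied by 32 per group at 80% power; and that the full 10% translates into missing second catheterisations. Relaxing any of them, or adjusting for baseline, narrows the gap and may close it. The primary endpoint is unaffected.

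**What to change.** - **Section 11.6:** replace the unconditional adequacy statement with the conditional figures. With 66 in the stratum, PA-pressure power is about 81% with complete pairs and about 77% (unadjusted) if 10% lack the Week 16 catheterisation; pulmonary vascular resistance stays above 80% in both cases.
- **Section 6:** state that 64 randomised gives 80% power for PA pressure only if all 64 have paired catheterisations.

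The cost is two sentences and a slightly less favourable stated figure. No patients are added, and no new analysis is needed because section 11.2.2 already plans ANCOVA-type models for haemodynamics.

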### 11.7 Statistical Estimates for Genetic Analysis

We will be particularly interested in evaluating a number of potential genetic risk factors for PH in individuals with SCD. The power of the study to find a significant difference between PH proportions in sickle cell patients with and without a genetic factor will depend on the numbers of cases with and without the factor, who have PH. For example, the variant VCAM1 G1238C has an estimated prevalence of 9% in both SS disease

populations and healthy African American populations in the USA. If 27 of 300 sickle cell cases have the variant and the true prevalence of PH is 30% in cases who do not have the variant, the prevalence of PH in cases who have the variant would have to be approximately 0.59 – i.e., the relative risk would have to be essentially 2 – in order for the study to have 80% power to find a significant increase. The table below shows the power of a study of 300 sickle cell patients to find a significant difference in PH prevalence between sickle cell patients with and without a genetic factor, by a z-test at a two-sided 5% level, as a function of the observed proportion of cases with the factor and the relative risk (RR) of PH in patients with the factor. True PH prevalence in the group of 300 sickle cell patients is assumed to be 30%, so that prevalence rates in patients with and without the factor depend on RR and the prevalence of the factor.

**Table 7. Relative Risk Ratio**

| Observed prevalence of genetic factor in sickle cell cases | Power (%) if relative risk (RR) of PH = |     |      |
|------------------------------------------------------------|-----------------------------------------|-----|------|
|                                                            | 1.5                                     | 2.0 | 2.5  |
| 5%                                                         | 24                                      | 64  | 93   |
| 10%                                                        | 38                                      | 85  | 99   |
| 15%                                                        | 47                                      | 93  | 99.8 |
| 20%                                                        | 54                                      | 96  | 99.9 |

The power is high (approximately 85% or higher) for genetic factors that are present in 10% or more of the sickle cell patients and have RR at least 2.

We intend for samples from this population to become a genetic archive to be used as a resource for analysis of many different genetic susceptibility factors. We have no preformed hypotheses about associations of specific genetic factors. Therefore, associations from this study will mainly serve to generate hypotheses to be tested in future studies.

## 12 HUMAN SUBJECT PROTECTION

### 12.1 Rationale for Subject Selection

Subjects of both genders will be considered for inclusion in this study. Because sickle cell anemia is primarily a disease affecting African Americans, most if not all of the subjects will be African American. Cognitively impaired and institutionalized persons will not participate in this study. Because this is a multi-Center trial, recruitment strategies may vary across sites. Subjects may be recruited through advertisement by the NIH Clinical Research Volunteer Program, the Patient Recruitment and Referral Center and through existing contacts with sickle cell individuals, support groups, and clinics. Additionally, recruitment may be a part of the general intake and may include measuring of vital signs and gathering of interim history. Criteria for exclusion or withdrawal from the study are based on the presence of other disease processes that may interfere with the interpretation of our results or situations that may be harmful to the healthy subjects.

## **12.2 Participation of Children**

Children 12 years of age and older will be included in this study per §46.405 Research involving greater than minimal risk but presenting the prospect of direct benefit to the individual subject. “DHHS will conduct or fund research in which the IRB finds that more than minimal risk to children is presented by an intervention or procedure that holds out the prospect of direct benefit for the individual subject, or by a monitoring procedure that is likely to contribute to the subject’s well-being, only if the IRB finds that:

- (a) the risk is justified by the anticipated benefit to the subjects;
- (b) the relation of the anticipated benefit to the risk is at least as favorable to the subjects as that presented by available alternative approaches; and
- (c) adequate provisions are made for soliciting the assent of the children and permission of their parents or guardians, as set forth in §46.408.

Heart catheterization is routinely performed for the diagnosis of pulmonary hypertension in pediatric patients. In addition, several centers perform follow-up catheterizations to assess response to therapy, guide therapeutic decisions and to provide prognostic information. Therefore, this follow-up measurement is necessary to help determine the effectiveness of the treatment in this research study. Therefore, for the purposes of this research, the second heart catheterization has been classified as research related and presents the prospect of direct benefit.

